#### **4.1.2 Secondary Outcome measures:**

- (i) Practicality of a home-based sleep test based on the experience of the participants as recorded by the research assistant during the sleep studies;
- (ii) Economic analysis comparing costs of a home-based sleep test with polysomnography for diagnosis of SRBDs in tetraplegics and paraplegics.
- (iii) STOP-Bang questionnaire will be used to screen participants without (score <3) or with symptoms or signs of SRBDs. A higher STOP-Bang score is associated with a greater degree of SRBD.

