### **3.2 Secondary study objectives:**

- (1) To confirm that a home-based sleep study is a feasible alternative for diagnosis of SRBDs in tetraplegics and paraplegics;
- (2) To compare the costs of a home-based sleep study with the conventional polysomnography in an overnight sleep clinic using cost-minimization analysis.

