#### **4.2 Description of the type/design of the study**

This is 3-year cross-sectional, prospective study.

- (1) Individuals with SCI frequently decline to stay overnight to complete formal polysomnography due to their concerns about availability of proper support, funding for attendants and the accessibility of the sleep disorder clinics. Given this, we decided to use a home-based or hospital-unattended sleep test (ResMed ApneaLink Air™) that is a practical, less costly, validated and reliable surrogate for diagnosis of the SRBDs. A trained research assistant from Sunnybrook Health Science Centre with expertise on the setting up and use of ResMed ApneaLink™, Bittium Faros™ 180 and Caretaker™ Medical cNIBP monitor devices will be available to assist the participants who have questions or problems with setting up the sleep apnea testing. The process for the technical support for the home based-sleep study will include the following steps:
  - (a) The research assistant from Sunnybrook Health Science Centre will receive a notification by phone from the research coordinator from Lyndhurst stating that a new participant will undergo home-based sleep studies. The study participant identifying number (i.e. “study participant ID #...”) along with their address and minimal clinical information (only level and severity of spinal cord injury) will be provided.
  - (b) The study participant will receive the name and phone number of the research assistant from Sunnybrook Health Science Centre and will be instructed to call them if there are any questions or concerns only during home-based sleep study (12 hours overnight support).
  - (c) If the study participant is unable to set up the home-based sleep study devices, they will be offered to receive a visit from the research assistant at their residence. If the study participant agrees, the research assistant will provide technical support at their residence.

Untreated sleep-related breathing disorders as an aggravating factor for neuropathic pain, cardiovascular dysfunction and spasticity following spinal cord injury

If the study participant disagrees and the setting up is not possible, the study participant will be withdrawn from the study.

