- (d) At discretion and expenses of the research assistant and [name] (co-investigator at Sunnybrook Health Science Centre, the home-based sleep study devices can be either send by especial and secure courier (e.g. FEDEX) or picked up by the research assistant at the study participant's residence on next the day after the test. The study participant must agree with the latter option before the research assistant can drop by their residence. All the costs for either option are included in the price for the service as per the revised inter-institutional agreement.
- (e) The research assistant must properly destroy all PHI right after completing of the home-based sleep studies. The only information that should be maintained includes the study participant ID number and data on how many times and the reasons for phone calls and/or visit to provide technical support.

(2) Individuals living with SCI are often on pharmacologic treatment for neuropathic pain and/or spasticity. Given their potential confounding effect, we will collect information on the medicaments taken at the time of the studies in order to properly analyze the results of both studies.

(3) All the laboratory blood tests will be carried out by a company that provides high-quality services using standardized assays and methods across Canada. This will facilitate the comparisons and interpretation of the results from this research project.

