### 4.3 Study Procedure

Table 1. Study Visits

| Event of Assessment                                                                                | Visit 1(Screening Visit) | Visit 2(Assessment after ApneaLink™ –home sleep test) |
|----------------------------------------------------------------------------------------------------|--------------------------|-------------------------------------------------------|
| Eligibility Screen                                                                                 | X                        |                                                       |
| STOP-Bang questionnaire                                                                            | X                        |                                                       |
| Visual Analog Scale for pain                                                                       | X                        |                                                       |
| Enrollment & ApneaLink Sleep Breathing, Bittium Faros™ 180 and Caretaker™ Medical cNIBP Monitoring | X                        |                                                       |
| Demographics                                                                                       | X                        |                                                       |
| History of Injury                                                                                  | X                        |                                                       |
| General Health History                                                                             | X                        |                                                       |
| Laboratory blood tests (CRP and CBC)                                                               |                          | X                                                     |
| Participants' experience on the use of a home-based sleep test                                     |                          | X                                                     |
| Modified Ashworth Scale                                                                            | X                        |                                                       |

Untreated sleep-related breathing disorders as an aggravating factor for neuropathic pain, cardiovascular dysfunction and spasticity following spinal cord injury

Visit 1 and 2 will each last approximately an hour.

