## **7. Statistics**

The baseline characteristics and outcomes measures among the four study groups will be analyzed using the Kruskal-Wallis test (non-parametric data) or ANOVA (parametric data). Study groups will also be compared using Fisher exact test regarding categorical variables. The costs of the home-based sleep study will be compared to the costs of the polysomnography using Mann-Whitney U test. Sample size and feasibility: Using pain (VAS) as the primary outcome measure, an estimated sample size of 10 subjects per group is required to detect a "minimal clinically important difference" of at least 25 mm in the VAS with a minimum power of 90% and a significance of 5% for 2-sided comparison tests.

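### The home-test feasibility objective is to be confirmed from participants' recorded experience alone; no outcome counts successful set-up or scoreable recordings, and set-up failures can leave the denominator

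*Protocol*

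**What the plan says.** Protocol 3.2, secondary objective 1, is "To confirm that a home-based sleep study is a feasible alternative for diagnosis of SRBDs in tetraplegics and paraplegics". The outcome that answers it is item (i) in 4.1.2: "Practicality of a home-based sleep test based on the experience of the participants as recorded by the research assistant during the sleep studies". The other two secondary outcomes are the cost comparison and the STOP-Bang score.

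Table 1 in 4.3 has one matching row, at Visit 2: participants' "experience on the use of a home-based sleep test". It has no row for whether the recording was completed or usable.

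Section 4.2 describes the support around the test. Participants have an overnight telephone contact. Those who cannot set up the devices are offered a home visit: "If the study participant agrees, the research assistant will provide technical support at their residence". For those who decline, "If the study participant disagrees and the setting up is not possible, the study participant will be withdrawn from the study". Step (e) keeps, with the participant ID number, "data on how many times and the reasons for phone calls and/or visit to provide technical support". The same section already describes the device as a "practical, less costly, validated and reliable surrogate for diagnosis of the SRBDs".

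Section 7 names one analysis specific to the home test: "The costs of the home-based sleep study will be compared to the costs of the polysomnography using Mann-Whitney U test".

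**The concern.** A home test is a feasible route to diagnosis if people can get it running and it returns a recording that can be scored. Reported experience bears on acceptability but measures neither of these. The objective therefore asks one question and its outcome answers another. The verb *confirm* also implies a result that could have gone the other way, and the protocol sets none.

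The withdrawal rule adds to the problem. A participant who cannot set up the devices and does not accept a visit is the plainest example of the test not being feasible, yet that person leaves the study and no outcome records the event as a failure.

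The protocol intends to act on the answer. Section 2.3.2 commits to reporting the feasibility of the home test and lists, as a project outcome, an outpatient and inpatient service for home-based or hospital-unattended sleep studies. Whoever plans that service needs to know how often the test gives a usable result and how much staff support that takes.

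**Working it through.** **The texts side by side.** The protocol states no figure for feasibility, so there is none to reproduce. Its only sample-size figure, 10 per group in Section 7, is for pain.

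| Needed for the objective | Where the protocol provides it |
|---|---|
| Outcome assigned to the objective | 4.1.2 (i): practicality, from recorded experience |
| Count of successful set-ups | Not an outcome; set-up failures who decline a visit are withdrawn (4.2 step (c)) |
| Count of scoreable recordings | Not an outcome; no row in Table 1 |
| Amount of staff support needed | Logged by participant ID (4.2 step (e)), but not named as an outcome |
| Result that would count against feasibility | None stated |

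**Effect of the denominator.** The inputs are 70 participants (4.4) and an assumed 56 usable recordings; the 56 is not in the protocol.

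- All assigned participants: 56/70 = 80%.
- Failures: 70 − 56 = 14. Let w of these be set-up withdrawals that are left out. The reported share becomes 56/(70 − w).
- w = 0 gives 56/70 = 80%; w = 14 gives 56/56 = 100%.

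So the same data could be summarised as anything from 80% to 100%, depending on how many failures were set-up withdrawals. The protocol gives no information on w.

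**Precision of the proposed outcome.** Exact (Clopper-Pearson) 95% limits for k successes in n: the lower limit is the 2.5% quantile of Beta(k, n − k + 1), and the upper limit is the 97.5% quantile of Beta(k + 1, n − k). The yields are assumed. The two sizes are the 70 invited (4.4) and the 40 shown for all participants in 4.3.

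| n | Usable | Share | Exact 95% CI |
|---|---|---|---|
| 70 | 56 | 80% | 68.7% to 88.6% |
| 70 | 63 | 90% | 80.5% to 95.9% |
| 40 | 32 | 80% | 64.4% to 90.9% |
| 40 | 36 | 90% | 76.3% to 97.2% |

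At 80% the half-width is (88.6 − 68.7)/2 ≈ 10 points at n = 70 and (90.9 − 64.4)/2 ≈ 13 points at n = 40. These widths follow from the sample size and would be the same under any wording. They show what the proposed outcome could deliver and do not measure the defect. Neither 70 nor 40 is established as the number tested at home, because the Protocol Summary and 4.2 also allow hospital-unattended testing.

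**What a criterion would demand.** As an example only, take the requirement that yield be shown to exceed 80% at a one-sided level of at most 0.05.

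| n | Usable recordings needed | Attained level | Power if true yield is 90% | Power if true yield is 95% |
|---|---|---|---|---|
| 70 | 62 | 0.044 | 74% | 99% |
| 40 | 37 | 0.028 | 42% | 86% |

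A rule that can fail is possible, but at the smaller size it has good power only if true yield is very high. That favours *estimate* over *confirm* unless the sponsor has a firm threshold in mind.

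**The case against.** The strongest reply is that the information is largely there already. Sections 4.3 and 4.4 class participants by severity from the ApneaLink result, so an unusable recording leaves someone who cannot be classed. Section 11 requires an explanation for any missing data. The log in 4.2 step (e) separates those who needed a call or visit from those who did not. On this view yield can be recovered and only a named summary is missing. The aim is also secondary and descriptive, and the primary comparisons are untouched.

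Much of this stands. It makes the fix cheap, and it rules out some stronger readings. A reader might infer that a participant with a comfortable night and an unusable recording would be scored a success, or that someone who needed a visit would count the same as someone who managed alone. The protocol defines no success score, and the log distinguishes the second pair. A reader might also infer that no result could ever tell against feasibility. Frequent calls, visits or withdrawals plainly could; what the protocol lacks is a statement in advance of what would.

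Interval methods and summaries by injury level are matters a SAP commonly settles, so their absence is not part of the finding. Nor is unaided first-night yield the only proper measure: the protocol describes a supported test and no repeat nights.

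What the reply does not remove is the mismatch itself. Which quantity answers an objective belongs in the protocol. Data that could answer it are not the same as an outcome that does, and nothing instructs the analyst to put withdrawn participants back in the denominator.

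**Conclusion.** The point holds as a mismatch between a secondary objective and its outcome. Followed as written, the plan could support a statement that home testing is confirmed as feasible without stating how many assigned participants got a scoreable recording, and with set-up failures left out.

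Its size is unknown, since it depends on how often set-up and recording fail and the protocol says nothing on either. The shift from 80% to 100% is an upper bound under an assumed 80% yield in 70 participants, not a forecast.

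A reader might take this as criticism that diagnostic accuracy goes untested. The documents do not support that reading: accuracy is taken as established in 4.2, and the objective speaks of feasibility. The claim is limited to technical yield and set-up success. The primary objectives and their sample size are unaffected. The change is worth making because it costs little and the result is meant to inform a service.

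**What to change.** Replace outcome (i) in 4.1.2 by the share of all participants assigned a home test whose ApneaLink recording can be scored. Count set-up withdrawals and unusable recordings as failures. The withdrawal rule itself need not change, only how those participants are counted.

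Report the share overall and split by support needed (none, telephone call, home visit) from the log in 4.2 step (e). Give a 95% CI and describe the result for tetraplegia and paraplegia, since the objective names both. State how many participants were assigned a home test rather than a hospital-unattended one, so that the denominator is fixed. Keep participants' experience as supporting description. In 3.2 (1), change *confirm* to *estimate*, or state beforehand what result would count as feasible.

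The cost is a protocol amendment to a few lines and a count from recordings and logs already kept. The downside is a figure that may look less favourable than a narrative and will be imprecise: roughly 10 to 13 points either side at an 80% yield with 70 or 40 participants, and wider within each injury-level group.

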#### **4.2 Description of the type/design of the study**

This is 3-year cross-sectional, prospective study.

- (1) Individuals with SCI frequently decline to stay overnight to complete formal polysomnography due to their concerns about availability of proper support, funding for attendants and the accessibility of the sleep disorder clinics. Given this, we decided to use a home-based or hospital-unattended sleep test (ResMed ApneaLink Air™) that is a practical, less costly, validated and reliable surrogate for diagnosis of the SRBDs. A trained research assistant from Sunnybrook Health Science Centre with expertise on the setting up and use of ResMed ApneaLink™, Bittium Faros™ 180 and Caretaker™ Medical cNIBP monitor devices will be available to assist the participants who have questions or problems with setting up the sleep apnea testing. The process for the technical support for the home based-sleep study will include the following steps:
  - (a) The research assistant from Sunnybrook Health Science Centre will receive a notification by phone from the research coordinator from Lyndhurst stating that a new participant will undergo home-based sleep studies. The study participant identifying number (i.e. “study participant ID #...”) along with their address and minimal clinical information (only level and severity of spinal cord injury) will be provided.
  - (b) The study participant will receive the name and phone number of the research assistant from Sunnybrook Health Science Centre and will be instructed to call them if there are any questions or concerns only during home-based sleep study (12 hours overnight support).
  - (c) If the study participant is unable to set up the home-based sleep study devices, they will be offered to receive a visit from the research assistant at their residence. If the study participant agrees, the research assistant will provide technical support at their residence.

Untreated sleep-related breathing disorders as an aggravating factor for neuropathic pain, cardiovascular dysfunction and spasticity following spinal cord injury

If the study participant disagrees and the setting up is not possible, the study participant will be withdrawn from the study.

- (d) At discretion and expenses of the research assistant and [name] (co-investigator at Sunnybrook Health Science Centre, the home-based sleep study devices can be either send by especial and secure courier (e.g. FEDEX) or picked up by the research assistant at the study participant's residence on next the day after the test. The study participant must agree with the latter option before the research assistant can drop by their residence. All the costs for either option are included in the price for the service as per the revised inter-institutional agreement.
- (e) The research assistant must properly destroy all PHI right after completing of the home-based sleep studies. The only information that should be maintained includes the study participant ID number and data on how many times and the reasons for phone calls and/or visit to provide technical support.

(2) Individuals living with SCI are often on pharmacologic treatment for neuropathic pain and/or spasticity. Given their potential confounding effect, we will collect information on the medicaments taken at the time of the studies in order to properly analyze the results of both studies.

(3) All the laboratory blood tests will be carried out by a company that provides high-quality services using standardized assays and methods across Canada. This will facilitate the comparisons and interpretation of the results from this research project.

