## **10. Ethics**

### **10.1 Recruitment**

Participants will be recruited using posters placed throughout the University Health Network. Inpatients at Toronto Rehab-Lyndhurst Centre will also be recruited using the TRI Central Recruitment Services (CRS) to identify potential participants. Furthermore, potential participants will be identified by the member of the potential subject's clinical team (e.g. medical doctor). The clinical team member and/or CRS Patient Liaison will identify potential candidates based on the subject's eligibility criteria (inclusion/exclusion). The clinical team member or CRS Patient Liaison will ask the eligible subject if he/she is interested to hear about research; if yes, then they will send a referral to the research coordinator. In this way, the subject's confidentiality is not breached.

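### A participant who cannot set up the home test and declines a visit is withdrawn before the experience assessment, and nothing says this counts as a failure for the feasibility objective

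*Protocol*

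**What the plan says.** All references are to the protocol; no SAP is at hand.

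- **Section 4.2, steps (b) and (c).** Participants have overnight telephone support. Those who cannot set up the devices are helped further: "they will be offered to receive a visit from the research assistant at their residence". If that is refused: "If the study participant disagrees and the setting up is not possible, the study participant will be withdrawn from the study".
- **Section 4.2, step (e).** After the sleep studies the research assistant destroys the personal health information. What is kept is the participant's ID and a record of how many support calls or visits there were and why.
- **Section 3.2.** Secondary objective 1 is "To confirm that a home-based sleep study is a feasible alternative for diagnosis of SRBDs in tetraplegics and paraplegics". Secondary objective 2 is "To compare the costs of a home-based sleep study with the conventional polysomnography in an overnight sleep clinic using cost-minimization analysis".
- **Section 4.1.2 (i).** The matching outcome is "Practicality of a home-based sleep test based on the experience of the participants as recorded by the research assistant during the sleep studies".
- **Section 4.3, Table 1.** The row "Participants' experience on the use of a home-based sleep test" is marked only under Visit 2, the assessment that follows the home sleep test.
- **Section 4.3, text.** The cost of the home test is estimated from experience in this study. Failed attempts are neither included nor excluded.
- **Section 5.3.** The general withdrawal section does not mention set-up failure and does not say how data from withdrawn participants are used.

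**The concern.** For a test that is meant to work at home, not getting it running is among the clearest signs that it is not feasible for that person. The protocol treats this event as a reason to leave the study, not as an outcome. Because the experience item is scheduled after the test, participants with some of the worst experiences are the ones the schedule does not reach.

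An SAP could define a denominator later, but it could not recover experience data that were never collected. The withdrawal rule and the visit schedule decide what is collected, and both are fixed in the protocol.

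What is at stake is the credibility of secondary objective 1. The protocol plans to report feasibility (Section 2.3.2) and lists a home or hospital-unattended sleep-test service among its intended outcomes. A figure based only on participants who got the devices running would make the case for that service look stronger than it is. The three primary association objectives in Section 3.1 do not depend on this point.

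**Working it through.** The protocol states no completion rate, failure rate or feasibility threshold, so there is no figure to reproduce. The check has two parts.

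**1. The passages side by side**

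| Question | What the protocol gives |
|---|---|
| What happens after set-up failure and a declined visit? | Withdrawal (Section 4.2, step c) |
| When is experience collected? | Visit 2, after the test (Table 1), but during the sleep studies according to Section 4.1.2 (i) |
| What survives for a withdrawn participant? | ID, and the number of and reasons for support calls and visits (Section 4.2, step e) |
| Does that log feed the feasibility outcome? | Not stated |
| Do withdrawn participants count as failures? | Not stated |
| Do failed attempts enter the home-test cost? | Not stated |

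The log as described has no field for the set-up result, for a refused visit or for experience. A participant who gives up without calling leaves nothing in it.

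**2. Direction and possible size**

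Let N be the number attempting the home test, w the number withdrawn for set-up failure and s the number completing it.

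- Withdrawn dropped: s / (N − w)
- Withdrawn kept as failures: s / N

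Whenever w and s are above 0, the first is larger than the second, so dropping them can only push the figure up.

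Inputs: N = 70, the number to be invited (Section 4.4), taken here as all attempting the home test. The values of w are assumptions for illustration. With no other failures, s = N − w:

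| w (assumed) | Dropped | Kept |
|---|---|---|
| 4 | 66/66 = 100% | 66/70 = 94.3% |
| 7 | 63/63 = 100% | 63/70 = 90.0% (95% CI 81% to 96%) |
| 14 | 56/56 = 100% (94% to 100%) | 56/70 = 80.0% (69% to 89%) |
| 21 | 49/49 = 100% | 49/70 = 70.0% (58% to 80%) |

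Intervals are Clopper-Pearson.

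The 100% depends on assuming no other failures. If about 10% of those who remain also fail for another reason:

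- w = 7: 57/63 = 90.5% dropped, 57/70 = 81.4% kept, a gap of 9.1 points.
- w = 14: 50/56 = 89.3% dropped, 50/70 = 71.4% kept, a gap of 17.9 points.

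So the upward shift does not depend on that assumption. Section 4.3 still works with 40 participants. At the same failure proportions the percentages are unchanged: 36/40 = 90% and 32/40 = 80%.

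**Cost.** The protocol does not exclude failed attempts, so no bias in cost can be derived from it. Only if an analyst left them out, and only if a failed attempt costs as much as a completed one, would cost per completed test be understated, by 70/63 = 1.11 (w = 7) or 70/56 = 1.25 (w = 14).

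**The case against.** The strongest reply is that the protocol nowhere removes these participants from the feasibility analysis. Several points support it:

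- The support log is kept by ID, with no exception for those withdrawn, and Section 11 requires an explanation for any missing data. A participant who phones for help leaves a trace.
- Section 4.1.2 (i) says the research assistant records experience during the sleep studies, so some experience may be noted before Visit 2.
- The group is narrow. Failing unaided does not trigger withdrawal; the participant must also decline a visit. Those who accept one stay in, with the visit logged.
- The outcome is participant experience, not a completion rate, and how withdrawn participants are counted is commonly left to the SAP.

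Most of this stands, and it limits the point. Removal of the failures is a risk that the protocol leaves open, not something it states. The reply does not answer the collection problem. The log holds no experience item and no set-up outcome, it is not tied to the feasibility result, and the two statements about when experience is recorded disagree.

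A reader might go further and infer that feasibility cannot fail. The documents do not support that: poor reported experience, heavy use of support or unusable recordings among those who remain could all show infeasibility. A reader might also infer that failed attempts are taken out of the cost estimate, but Section 4.3 does not say so.

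**Conclusion.** The point holds in a limited form. The protocol withdraws participants whose set-up failure is a negative result for secondary objective 1, at a stage when they would be expected to miss the scheduled experience assessment, and it does not say that they count as failures. If they are dropped, feasibility is overstated.

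The direction is certain under that condition; the size is not known. The illustration (a true 90% or 80% read as 100%) rests on assumed numbers of 7 and 14 failures among 70 attempts, no other failures, and a completion rate as the measure, which the protocol does not define. Because only those who also decline a visit are affected, the real number could be smaller.

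On cost, the supportable statement is that the protocol does not say whether failed attempts count.

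Two further inferences are tempting and should not be made. One is that those lost would mainly have higher cervical injuries: no section gives set-up failure by injury level or describes the help available at home. The other is that tests done in hospital inflate the home result: inpatients are recruited (Section 10.1), but nothing pools their tests into the feasibility outcome.

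This is a worthwhile, inexpensive correction to a secondary objective, not a threat to the primary analyses.

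**What to change.** 1. In Section 4.2, step (c), replace the withdrawal with wording such as: *the participant is recorded as a home-test set-up failure, stays in the feasibility denominator, is asked the Visit 2 experience items by phone if they agree, and is excluded only from analyses that need sleep data.*
2. State that the support log in step (e) contributes to the feasibility result, and add the set-up outcome and a refused visit to what is kept.
3. In Section 4.3, state that the costs of failed attempts are included in the home-test cost estimate.
4. Reconcile Section 4.1.2 (i) with Table 1 on when experience is recorded.

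Cost: a short amendment, one CRF field and a brief phone call for each affected participant. No extra visit is needed, and a participant who wants to leave the study can still do so under Section 5.3.
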